**TIME TO ESRD: STATISTICAL ANALYSIS (PH MODEL)**

| Covariate                 | Parameter Estimate | Standard Error | p-value |
|---------------------------|--------------------|----------------|---------|
| Age                       | x.xx               | x.xx           | x.xxx   |
| Sex                       | x.xx               | x.xx           | x.xxx   |
| Baseline Serum Creatinine | x.xx               | x.xx           | x.xxx   |

  

| Treatment Comparison      | Hazard Ratio (SE) | 95% CI for the Hazard Ratio | p-value a |
|---------------------------|-------------------|-----------------------------|----------------------|
| Octreotide-LAR vs Placebo | xx.x (xx.x)       | xx.x to xx.x                | x.xxx                |

**Population: Full Analysis Set**

a A p-value <0.05 will be considered to be evidence of a significant difference between the treatment groups

TABLE 3.54.1

**TIME TO DOUBLING OF SERUM CREATININE OR ESRD: SUMMARY**

|                                             | Octreotide-LAR      | Placebo             |
|---------------------------------------------|---------------------|---------------------|
| Number of Patients                   | xx           | xx           |
| Number of patients events-free              |                     |                     |
| 6 months                                    | xx (xx%)            | xx (xx%)            |
| 12 months                                   | xx (xx%)            | xx (xx%)            |
| ●                                           | ●                   | ●                   |
| ●                                           | ●                   | ●                   |
| ●                                           | ●                   | ●                   |
| Median time to event (95% CI a ) | xx.x (xx.x to xx.x) | xx.x (xx.x to xx.x) |
| Number (%) of censored patients             | xx (xx%)            | xx (xx%)            |

**Population: Full Analysis Set**

a Calculated using Greenwood’s formula

TABLE 3.54.2

**TIME TO DOUBLING OF SERUM CREATININE OR ESRD: STATISTICAL ANALYSIS (PH MODEL)**

| Covariate | Parameter Estimate | Standard Error | p-value |
|-----------|--------------------|----------------|---------|
|-----------|--------------------|----------------|---------|

|                           |      |      |       |
|---------------------------|------|------|-------|
| Age                       | X.XX | X.XX | X.XXX |
| Sex                       | X.XX | X.XX | X.XXX |
| Baseline Serum Creatinine | X.XX | X.XX | X.XXX |

| Treatment Comparison      | Hazard Ratio
(SE) | 95% CI for the
Hazard Ratio | p-value a |
|---------------------------|----------------------|--------------------------------|----------------------|
| Octreotide-LAR vs Placebo | xx.x (xx.x)          | xx.x to xx.x                   | x.xxx                |

**Population: Full Analysis Set**

a A p-value <0.05 will be considered to be evidence of a significant difference between the treatment groups

TABLE 3.55.1

TIME TO OVERALL MORTALITY: SUMMARY

|                                             | Octreotide-LAR      | Placebo             |
|---------------------------------------------|---------------------|---------------------|
| Number of Patients                   | xx           | xx           |
| Number of patients events-free              |                     |                     |
| 6 months                                    | xx (xx%)            | xx (xx%)            |
| 12 months                                   | xx (xx%)            | xx (xx%)            |
| ●                                           | ●                   | ●                   |
| ●                                           | ●                   | ●                   |
| ●                                           | ●                   | ●                   |
| Median time to event (95% CI a ) | xx.x (xx.x to xx.x) | xx.x (xx.x to xx.x) |
| Number (%) of censored patients             | xx (xx%)            | xx (xx%)            |

Population: Full Analysis Set

a Calculated using Greenwood’s formula

TABLE 3.55.2

TIME TO OVERALL MORTALITY: STATISTICAL ANALYSIS (PH MODEL)

| Covariate                 | Parameter Estimate | Standard Error | p-value |
|---------------------------|--------------------|----------------|---------|
| Age                       | x.xx               | x.xx           | x.xxx   |
| Sex                       | x.xx               | x.xx           | x.xxx   |
| Baseline Serum Creatinine | x.xx               | x.xx           | x.xxx   |

  

| Treatment Comparison      | Hazard Ratio (SE) | 95% CI for the Hazard Ratio | p-value a |
|---------------------------|-------------------|-----------------------------|----------------------|
| Octreotide-LAR vs Placebo | xx.x (xx.x)       | xx.x to xx.x                | x.xxx                |

Population: Full Analysis Set

a A p-value <0.05 will be considered to be evidence of a significant difference between the treatment groups

TABLE 3.56.1

TIME TO CARDIOVASCULAR MORTALITY: SUMMARY

|                                             | Octreotide-LAR      | Placebo             |
|---------------------------------------------|---------------------|---------------------|
| Number of Patients                          | xx                  | xx                  |
| Number of patients events-free              |                     |                     |
| 6 months                                    | xx (xx%)            | xx (xx%)            |
| 12 months                                   | xx (xx%)            | xx (xx%)            |
| ●                                           | ●                   | ●                   |
| ●                                           | ●                   | ●                   |
| ●                                           | ●                   | ●                   |
| Median time to event (95% CI a ) | xx.x (xx.x to xx.x) | xx.x (xx.x to xx.x) |
| Number (%) of censored patients             | xx (xx%)            | xx (xx%)            |

Population: Full Analysis Set

a Calculated using Greenwood’s formula

TABLE 3.56.2

**TIME TO CARDIOVASCULAR MORTALITY: STATISTICAL ANALYSIS (PH MODEL)**

| Covariate                 | Parameter Estimate | Standard Error | p-value |
|---------------------------|--------------------|----------------|---------|
| Age                       | x.xx               | x.xx           | x.xxx   |
| Sex                       | x.xx               | x.xx           | x.xxx   |
| Baseline Serum Creatinine | x.xx               | x.xx           | x.xxx   |

  

| Treatment Comparison      | Hazard Ratio (SE) | 95% CI for the Hazard Ratio | p-value a |
|---------------------------|-------------------|-----------------------------|----------------------|
| Octreotide-LAR vs Placebo | xx.x (xx.x)       | xx.x to xx.x                | x.xxx                |

**Population: Full Analysis Set**

a A p-value <0.05 will be considered to be evidence of a significant difference between the treatment groups

TABLE 3.57.1

**TIME TO NON-CARDIOVASCULAR MORTALITY: SUMMARY**

|                |         |
|----------------|---------|
| Octreotide-LAR | Placebo |
|----------------|---------|

| Number of Patients                          | xx                  | xx                  |
|---------------------------------------------|---------------------|---------------------|
| Number of patients events-free              |                     |                     |
| 6 months                                    | xx (xx%)            | xx (xx%)            |
| 12 months                                   | xx (xx%)            | xx (xx%)            |
| •                                           | •                   | •                   |
| •                                           | •                   | •                   |
| •                                           | •                   | •                   |
| Median time to event (95% CI a ) | xx.x (xx.x to xx.x) | xx.x (xx.x to xx.x) |
| Number (%) of censored patients             | xx (xx%)            | xx (xx%)            |

**Population: Full Analysis Set**

a Calculated using Greenwood’s formula

TABLE 3.57.2

**TIME TO NON-CARDIOVASCULAR MORTALITY: STATISTICAL ANALYSIS (PH MODEL)**

| Covariate                 | Parameter Estimate | Standard Error | p-value |
|---------------------------|--------------------|----------------|---------|
| Age                       | x.xx               | x.xx           | x.xxx   |
| Sex                       | x.xx               | x.xx           | x.xxx   |
| Baseline Serum Creatinine | x.xx               | x.xx           | x.xxx   |

| Treatment Comparison      | Hazard Ratio
(SE) | 95% CI for the
Hazard Ratio | p-value a |
|---------------------------|----------------------|--------------------------------|----------------------|
| Octreotide-LAR vs Placebo | xx.x (xx.x)          | xx.x to xx.x                   | x.xxx                |

**Population: Full Analysis Set**

a A p-value <0.05 will be considered to be evidence of a significant difference between the treatment groups

TABLE 4.1

**SUMMARY OF ADVERSE EVENTS**

|                                                                               | Octreotide-LAR | Placebo   |
|-------------------------------------------------------------------------------|----------------|-----------|
| Number of Patients                                                     | xx      | xx |
| No (%) of patients with an adverse event                                      | xx (xx%)       | xx (xx%)  |
| No (%) of patients with a serious adverse event                               | xx (xx%)       | xx (xx%)  |
| No (%) of patients with a non -serious adverse event                          | xx (xx%)       | xx (xx%)  |
| No (%) of patients with a severe adverse event                                | xx (xx%)       | xx (xx%)  |
| No (%) of patients with an event probably related to study drug               | xx (xx%)       | xx (xx%)  |
| No (%) of patients with an adverse event leading to permanent discontinuation | xx (xx%)       | xx (xx%)  |
| Average number of events per patient                                          | xx.x           | xx.x      |
| Average number of events per patient (with a least 1 event)                   | xx.x           | xx.x      |
| No (%) of deaths                                                              | xx (xx%)       | xx (xx%)  |

**Population: Full Analysis Set**

TABLE 4.2

**SUMMARY OF SERIOUS ADVERSE EVENTS**

|                                                                 | Octreotide-LAR | Placebo   |
|-----------------------------------------------------------------|----------------|-----------|
| Number of Patients                                       | xx      | xx |
| No (%) of patients with an adverse event                        | xx (xx%)       | xx (xx%)  |
| No (%) of patients with a severe adverse event                  | xx (xx%)       | xx (xx%)  |
| No (%) of patients with an event probably related to study drug | xx (xx%)       | xx (xx%)  |
| Average number of events per patient                            | xx.x           | xx.x      |
| Average number of events per patient (with a least 1 event)     | xx.x           | xx.x      |
| No (%) of deaths                                                | xx (xx%)       | xx (xx%)  |

**Population: Full Analysis Set**

TABLE 4.3

**FREQUENCY OF ADVERSE EVENTS BY BODY SYSTEM AND PREFERRED TERM**

|                           | Octreotide-LAR | Placebo   |
|---------------------------|----------------|-----------|
| Number of Patients | xx      | xx |
| Body System 1             | xx (xx%)       | xx (xx%)  |
| Preferred Term 1          | xx (xx%)       | xx (xx%)  |
| •                         | •              | •         |
| •                         | •              | •         |
| •                         | •              | •         |
| Preferred Term n          | xx (xx%)       | xx (xx%)  |
| •                         | •              | •         |
| •                         | •              | •         |
| •                         | •              | •         |
| Body System n             | xx (xx%)       | xx (xx%)  |
| Preferred Term 1          | xx (xx%)       | xx (xx%)  |
| •                         | •              | •         |
| •                         | •              | •         |
| •                         | •              | •         |
| Preferred Term n          | xx (xx%)       | xx (xx%)  |

**Population: Full Analysis Set**

TABLE 4.4

**FREQUENCY OF SERIOUS ADVERSE EVENTS BY BODY SYSTEM AND  
PREFERRED TERM**

|                           | Octreotide-LAR | Placebo   |
|---------------------------|----------------|-----------|
| Number of Patients | xx      | xx |
| Body System 1             | xx (xx%)       | xx (xx%)  |
| Preferred Term 1          | xx (xx%)       | xx (xx%)  |
| •                         | •              | •         |
| •                         | •              | •         |
| •                         | •              | •         |
| Preferred Term n          | xx (xx%)       | xx (xx%)  |
| •                         | •              | •         |
| •                         | •              | •         |
| •                         | •              | •         |
| Body System n             | xx (xx%)       | xx (xx%)  |
| Preferred Term 1          | xx (xx%)       | xx (xx%)  |
| •                         | •              | •         |
| •                         | •              | •         |
| •                         | •              | •         |
| Preferred Term n          | xx (xx%)       | xx (xx%)  |

**Population: Full Analysis Set**

*[Note: Tables 4.7 to 4.9 will be produced using this template. See Section 4 of Statistical Analysis Plan for table titles]*

TABLE 4.5

PATIENT DEATHS

|                      | Octreotide-LAR | Placebo  |
|----------------------|----------------|----------|
| Number of Patients   | xx             | xx       |
| Number (%) of Deaths | xx (xx%)       | xx (xx%) |
| Reason for Death     |                |          |
| Reason 1             | xx (xx%)       | xx (xx%) |
| •                    | •              | •        |
| •                    | •              | •        |
| •                    | •              | •        |
| Reason n             | xx (xx%)       | xx (xx%) |

Population: Full Analysis Set

TABLE 4.6

**LABORATORY TESTS AT BASELINE (VISIT B1-WEEK 0)**

| Laboratory Parameter | Octreotide-LAR | Placebo        |
|----------------------|----------------|----------------|
| Creatinine (mg/dl)   |                |                |
| Mean (sd)            | xxx.x (xxx.xx) | xxx.x (xxx.xx) |
| Median               | xxx.x          | xxx.x          |
| Minimum              | xxx            | xxx            |
| Maximum              | xxx            | xxx            |
| n                    | xx             | xx             |
| N §       | xx (xx%)       | xx (xx%)       |
| A §       | xx (xx%)       | xx (xx%)       |
| •                    | •              | •              |
| •                    | •              | •              |
| •                    | •              | •              |
| •                    | •              | •              |
| (%)                  |                |                |
| Mean (sd)            | xxx.x (xxx.xx) | xxx.x (xxx.xx) |
| Median               | xxx.x          | xxx.x          |
| Minimum              | xxx            | xxx            |
| Maximum              | xxx            | xxx            |
| n                    | xx             | xx             |
| Low                  | xx (xx%)       | xx (xx%)       |
| Normal               | xx (xx%)       | xx (xx%)       |
| High                 | xx (xx%)       | xx (xx%)       |

**Population: Full Analysis Set**

**§ Note: N=Normal or abnormal, but not clinically relevant; A=Abnormal and clinically relevant**

TABLE 4.7

**LABORATORY TEST SHIFT TABLE-CREATININE (mg/dl)**

| Octreotide-       |                 |                 |                 |                 |
|-------------------|-----------------|-----------------|-----------------|-----------------|
| LAR               |                 |                 |                 |                 |
|                   | NN § | NA § | AN § | AA § |
| Visit B2 (Week 1) | xx              | xx              | xx              | xx              |
| Visit B4 (Week 3) | xx              | xx              | xx              | xx              |
| Visit B5 (Week 6) | xx              | xx              | xx              | xx              |
| Visit B6 (Week 9) | xx              | xx              | xx              | xx              |
| ●                 | ●               | ●               | ●               | ●               |
| ●                 | ●               | ●               | ●               | ●               |
| ●                 | ●               | ●               | ●               | ●               |
| Final Visit       | xx              | xx              | xx              | xx              |

  

| Placebo           |                 |                 |                 |                 |
|-------------------|-----------------|-----------------|-----------------|-----------------|
|                   | LL § | LN § | LH § | NL § |
| Visit B2 (Week 1) | xx              | xx              | xx              | xx              |
| Visit B4 (Week 3) | xx              | xx              | xx              | xx              |
| Visit B5 (Week 6) | xx              | xx              | xx              | xx              |
| Visit B6 (Week 9) | xx              | xx              | xx              | xx              |
| ●                 | ●               | ●               | ●               | ●               |
| ●                 | ●               | ●               | ●               | ●               |
| ●                 | ●               | ●               | ●               | ●               |
| Final Visit       | xx              | xx              | xx              | xx              |

**Population: Full Analysis Set****§ Note: N=Normal or abnormal, but not clinically relevant; A=Abnormal and clinically relevant***[Note: Tables 4.8 to 4.23 will be produced in a similar format]*

TABLE 4.24

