The secondary objectives are to compare, among the two groups, absolute and relative changes in renal and liver volume parameters (at month 0, 12 and 36) as well as in functional and biochemical parameters by quarterly clinical visits during the 36 month follow-up. In particular, the following parameters will be assessed:

- Total kidney volume (at 3-years)
- Total renal cyst volume\*
- Total renal parenchyma volume\*
- Total renal intermediate volume\*
- Total liver and liver cyst volumes\*

*\*When feasible, by minimized radio contrast agent administration during CT acquisition*

- GFR decline (as assessed by serial measurements of the plasma iohexol clearance at month 0 and, every 6 months thereafter)
- Slope of eGFR (by MDRD 4 variable equation)
- Progression to the combined end point of doubling of serum creatinine and/or ESRD (*ESRD: need for chronic renal replacement therapy by dialysis or transplantation established on the basis of standard clinical criteria*)
- Progression to ESRD considered as a single endpoint
- Systolic, diastolic and mean blood pressure
- 24 h urinary protein excretion rate (at month 0 and every six months thereafter)
- Urinary osmolality (assessed from urine sodium, urea and glucose concentration on 24 hr urine samples)
- Morning spot urine sample (proteins, albumin, creatinine)
- Serum Insulin Growth Factor-1 (IGF-I)
- 24 h urinary phosphorus, creatinine and creatinine clearance
- Gallbladder sand/stones and renal stones (by ultrasonography).

In a subgroup of patients referred to the Clinical Research Center for Rare Diseases 'Aldo e Cele Daccò' and/or other institutions where these evaluations are feasible the

following other secondary objectives are to compare, among the two groups the quality of life and the societal costs by submitting to consenting patients a *Quality of life (QoL) Questionnaire* - Version 1 of SF-36 (QoL SF-36 V1™ Questionnaire) validated in Italy – and a *Short-Form-Health and Labour Questionnaire (SFHLQ)*. (See Appendix 2).

Furthermore, for exploratory purposes only, the treatment effect on endothelin and MCP-1 urinary excretion rate (overnight urine sample), in a subgroup (pending on study findings and fund availability).

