### **3.4.3 Laboratory Tests (Tables 4.6 to 4.23)**

Table 4.6 will contain summary statistics by treatment group for the complete collection of laboratory variables collected at Week 0. The statistics used will be mean(sd), median, minimum, and maximum and frequencies of normal or abnormal but not clinically relevant values (N) and abnormal and clinically relevant values (P).

Summary statistics will be provided for the 'selected' laboratory tests and for the change from baseline in the 'selected' laboratory tests at

each visit and also for the final visit (last value available) in Tables 4.6 to 4.23.

Individual patient laboratory data will be presented in Appendix 19.

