- 3.27.1 24 Hours Urine Collection (up to Table 3.33.3)
- 3.34.1 Spot Morning Urine (up to Table 3.38. 3)
- 3.39.1 TKV and absolute and percent changes in TKV (up to Table 3.39.3)
- 3.40.1 htTKV and absolute and percent changes in htTKV (up to Table 3.40.3)
- 3.41.1 Lipid Profile (up to Table 3.44.3)
- 3.45.1 Hemochrome (up to Table 3.49.3)
- 3.50.1 Total slope of  $eGFR_{\text{mdrd}}$  and  $Egfr_{\text{ckd-epi}}$  (up to Table 3.51.3)
- 3.52 Chronic slope of  $eGFR_{\text{mdrd}}$  and  $Egfr_{\text{ckd-epi}}$  (up to Table 3.53)
- 3.53.1 Time to ESRD and time to composite endpoint (up to Table 3.54.3)
- 3.55.1 Overall, Cardiovascular and Non-cardiovascular Mortality (up to Table 3.57.3)
- 3.58.1 Incidence of Major Cardiovascular Event (up to Table 3.58.2)
- 4.1 Summary of Adverse Events
- 4.2 Summary of Serious Adverse Events
- 4.3 Frequency of Adverse Events by Body System and Preferred Term
- 4.4 Frequency of Serious Adverse Events by Body System and Preferred Term
- 4.5 Death
- 4.6 Laboratory Tests at Baseline (Visit 2 - Month 0)
- 4.7 Laboratory Test Shift Table – Creatinine (mg/dl)
- 4.8 Laboratory Test Shift Table – Urea (mg/dl)
- 4.9 Laboratory Test Shift Table – Calcium (mg/dl)

- 4.10 Laboratory Test Shift Table – Sodium (mEq/l)
- 4.11 Laboratory Test Shift Table – Potassium (mEq/l)
- 4.12 Laboratory Test Shift Table – Phosphorous (mg/dl)
- 4.13 Summary Statistics for Change from Baseline – Creatinine (mg/dl)
- 4.14 Summary Statistics for Change from Baseline – Urea (mg/dl)
- 4.15 Summary Statistics for Change from Baseline – Calcium (mg/dl)
- 4.16 Summary Statistics for Change from Baseline – Sodium (mEq/l)
- 4.17 Summary Statistics for Change from Baseline – Potassium (mEq/l)
- 4.18 Summary Statistics for Change from Baseline – Phosphorous (mg/dl)
- 4.19 Urine Analysis Shift Table – Leukocytes
- 4.20 Urine Analysis Shift Table – Nitrates
- 4.21 Urine Analysis Shift Table – Ketones
- 4.22 Urine Analysis Shift Table – pH
- 4.23 Urine Analysis Shift Table – Glucose
- 4.24 Change From Baseline serum creatinine
- 4.25 Urine Analysis Shift Table – Hb
- 4.26 Urine Analysis Shift Table – Proteins
- 4.27 ECG Shift Table

## SECTION 5

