**SYSTOLIC BLOOD PRESSURE (mmHg) OVER TIME: SUMMARY**

|                                                             | Octreotide-LAR | Placebo        |
|-------------------------------------------------------------|----------------|----------------|
| Visit 2 (Month 0)                                           |                |                |
| Mean (sd)                                                   | xxx.x (xxx.xx) | xxx.x (xxx.xx) |
| Median                                                      | xxx.x          | xxx.x          |
| Minimum                                                     | xxx            | xxx            |
| Maximum                                                     | xxx            | xxx            |
| n                                                           | xx             | xx             |
| Visit 3 (Month 3)                                           |                |                |
| Mean (sd)                                                   | xxx.x (xxx.xx) | xxx.x (xxx.xx) |
| Median                                                      | xxx.x          | xxx.x          |
| Minimum                                                     | xxx            | xxx            |
| Maximum                                                     | xxx            | xxx            |
| n                                                           | xx             | xx             |
| Visit 4 (Month 6)                                           |                |                |
| Mean (sd)                                                   | xxx.x (xxx.xx) | xxx.x (xxx.xx) |
| Median                                                      | xxx.x          | xxx.x          |
| Minimum                                                     | xxx            | xxx            |
| Maximum                                                     | xxx            | xxx            |
| n                                                           | xx             | xx             |
| Visit 5 (Month 9)                                           |                |                |
| Mean (sd)                                                   | xxx.x (xxx.xx) | xxx.x (xxx.xx) |
| Median                                                      | xxx.x          | xxx.x          |
| Minimum                                                     | xxx            | xxx            |

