**SUMMARY STATISTICS FOR CHANGE FROM BASELINE-CREATININE (mg/dl)**

| Octreotide-LAR    |                |                      | Placebo        |                      |
|-------------------|----------------|----------------------|----------------|----------------------|
|                   | Absolute Value | Change from Baseline | Absolute Value | Change from Baseline |
| Visit B1 (Week 0) |                |                      |                |                      |
| Mean (sd)         | xx.x (xx.xx)   |                      | xx.x (xx.xx)   |                      |
| Median            | xx.x           |                      | xx.x           |                      |
| Minimum           | xx             |                      | xx             |                      |
| Maximum           | xx             |                      | xx             |                      |
| n                 | xx             |                      | xx             |                      |
| Visit B2 (Week 1) |                |                      |                |                      |
| Mean (sd)         | xx.x (xx.xx)   | xx.x (xx.xx)         | xx.x (xx.xx)   | xx.x (xx.xx)         |
| Median            | xx.x           | xx.x                 | xx.x           | xx.x                 |
| Minimum           | xx             | xx                   | xx             | xx                   |
| Maximum           | xx             | xx                   | xx             | xx                   |
| n                 | xx             | xx                   | xx             | xx                   |
| ●                 |                |                      |                |                      |
| ●                 |                |                      |                |                      |
| ●                 |                |                      |                |                      |
| ●                 |                |                      |                |                      |
| Final Visit       |                |                      |                |                      |
| Mean (sd)         | xx.x (xx.xx)   | xx.x (xx.xx)         | xx.x (xx.xx)   | xx.x (xx.xx)         |
| Median            | xx.x           | xx.x                 | xx.x           | xx.x                 |
| Minimum           | xx             | xx                   | xx             | xx                   |

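### The laboratory shift shell (Table 4.7) puts the two arms on different category scales and names weeks with no laboratory form: a minor error, confined to the safety tables

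*Supplement*

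**What the plan says.** **Shift shell.** Table 4.7 in SAP section 7 has one panel per arm. The octreotide columns are NN, NA, AN and AA; the placebo columns are LL, LN, LH and NL. The only key is "N=Normal or abnormal, but not clinically relevant; A=Abnormal and clinically relevant". The named rows run from "Visit B2 (Week 1" to "Visit B6 (Week 9", with Weeks 3 and 6 between them. Continuation dots and a Final Visit row follow. A note adds: "Tables 4.8 to 4.23 will be produced in a similar format".

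**SAP text.** Section 3.4.3 describes one two-level scale, summarised by treatment group: "frequencies of normal or abnormal but not clinically relevant values (N) and abnormal and clinically relevant values (P". The second level is lettered P there and A in the shell. Section 3.4.3 mentions summary statistics and change from baseline, but says nothing about shifts.

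**Visits.** The SAP introduction plans "functional and biochemical parameters by quarterly clinical visits during the 36 month follow-up". The efficacy shells, such as Table 3.3.1, go from Visit 2 (Month 0) to "Visit 3 (Month 3" and on in three-month steps. SAP section 4 lists Table 4.6 as "Laboratory Tests at Baseline (Visit 2 - Month 0", but the shell of that table is headed with Visit B1 and Week 0. The Table 4.24 shell (change from baseline in creatinine) also starts at B1 and B2.

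**The concern.** A shift table shows how many patients in each arm move from an acceptable to a clinically relevant abnormal value. That reading needs the same categories in both arms and rows at visits where blood was taken. The Table 4.7 shell gives neither.

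It is also the only specification of how the laboratory shift tables are built, because section 3.4.3 does not describe them. A programmer who follows the shell produces panels that cannot be set against each other. A programmer who departs from it must choose the scale, and the documents offer N/A, N/P and low/normal/high.

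**Working it through.** There is no figure in the plan to reproduce. The check sets the passages side by side, with some counting.

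**1. Categories**

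| Place | Scale | Letters defined there |
|---|---|---|
| Table 4.7, octreotide panel | two levels | N, A |
| Table 4.7, placebo panel | low/normal/high | footnote gives N and A only |
| Table 4.6 shell, creatinine | two levels | N, A |
| Table 4.6 shell, last parameter | low/normal/high | row labels in words |
| SAP 3.4.3 | two levels, by treatment group | N, P |

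The two panels of Table 4.7 share no column label. Even a restored NN column in the placebo panel would not mean the same thing. Under the footnote, N includes abnormal values that are not clinically relevant; on a low/normal/high scale those values fall under L or H.

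**2. Visits**

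- Blood laboratory forms run from v02 to v14: 14 − 2 + 1 = 13 visits, 12 of them after baseline.
- The other shells imply month = 3 × (visit number − 2). Visit 3 gives 3, Visit 7 gives 15 and Visit 14 gives 36. The CT forms at v02, v06 and v14 agree, falling at Months 0, 12 and 36.
- SAP 2.4 puts the three-month visit at day 91, and 91 / 7 = week 13.
- The shell rows fall on days 7 × 1 = 7, 7 × 3 = 21, 7 × 6 = 42 and 7 × 9 = 63.
- SAP 2.4 lists day 7 (one week) and day 30 (one month) before day 91. So Week 1 is a listed time point, but no laboratory form is shown for it. Days 21, 42 and 63 are not scheduled days.
- Days 21 and 63 lie inside the one-month window (20–40) and the three-month window (61–121). This does not rescue the rows, because SAP 3.2 classifies data by nominal visit and does not use windows.

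One caution on the visit numbers: SAP 3.3 calls the 12-month visit Visit 7, whereas the shells and the CT forms make it Visit 6. A numbering shifted by one could admit one early visit, at one week or one month. It would not create Weeks 3, 6 and 9.

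**3. Reach**

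The template note covers 4.8 to 4.23, which is 16 tables. By the SAP section 4 list these are:

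- 4.8–4.12: 5 laboratory shift tables
- 4.13–4.18: 6 change-from-baseline tables
- 4.19–4.23: 5 urine shift tables

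5 + 6 + 5 = 16. With Table 4.7 itself, the laboratory shift tables number 6: creatinine, urea, calcium, sodium, potassium and phosphorus. For the urine tables SAP 3.4.4 sets its own NN/NP/PN/PP scheme, the same in both arms.

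**The case against.** The fair defence is that this is leftover template text and that the governing section is sound. Section 3.4.3 sets a single scale with no arm-specific version, and asks for selected tests at each visit and at the last available value. On that view the only conflict in the text itself is a letter, P against A. This is largely right about intent. It does not mend the shell, because section 3.4.3 never describes the shift tables.

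A cut in the PDF is another possible defence. Neighbouring templates do lose columns on the right; in Table 3.2 the placebo block stops at six months. Truncation can remove columns but cannot turn a two-level scale into a three-level one, and the first placebo columns are already on low/normal/high. A reader might also count the low/normal/high transitions absent from the placebo panel. That count should not be used, since the missing columns may simply have been cut.

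Other stronger readings are tempting and are not supported:

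- *Months 3 to 36 are reduced to the Final Visit row.* The continuation dots leave room for them; they are unnamed, not excluded.
- *None of the named weeks belongs to the trial.* Week 1 stands in SAP 2.4.
- *L and H have no meaning anywhere.* The Table 4.6 shell spells out low, normal and high. What is missing is a key in Table 4.7 and a reason for the second scale.
- *Laboratory safety cannot be compared between the arms.* Table 3.8.1 gives creatinine by arm at quarterly visits, and its note extends that format to the hematochemistry tables. The change-from-baseline shell has the same layout for both arms, apart from its visit labels.

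**Conclusion.** The shell is wrong as written, and the point is minor. Followed literally, the categorical laboratory shifts in six safety tables (4.7 to 4.12) could not be compared between octreotide and placebo, and the four named rows would have no laboratory form behind them. Tables 4.6 and 4.24 share the wrong visit labels but not the split between arms. Continuous laboratory summaries and changes from baseline remain comparable, and no efficacy endpoint, test or analysis population depends on the point.

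This rests on three assumptions: that the printed CRF shows every laboratory form; that the visit numbering is that of the shells and CT forms; and that the section 4 list, not the template note, decides which tables are laboratory shift tables.

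**What to change.** 1. In Tables 4.7 to 4.12 use the two-level classification of SAP 3.4.3 in both arms, with the same four transition columns. Take it from the Assessment field that the CRF holds for each analyte at each laboratory visit. The printed form does not show the permitted values of that field, so confirm that they map to the two levels.
2. Choose one set of letters, N/A or N/P, and define it once for section 3.4.3 and the shells. SAP 3.4.4 uses N and P for negative and positive in urine, so reusing P invites confusion.
3. Replace the B-visit rows in Tables 4.6, 4.7–4.12 and the change-from-baseline tables. Use Visit 2 (Month 0) as baseline, then Visits 3 to 14 (Months 3 to 36) plus the last available value where post-baseline rows apply. Settle the Visit 6 or Visit 7 label for Month 12 at the same time.
4. Align the note on Tables 4.8 to 4.23 with the section 4 list. The note under Table 4.4, which assigns Tables 4.7 to 4.9 to the adverse event template, needs the same correction.

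The cost is an edit to the shells and one line in section 3.4.3, made before programming. No new data are needed.
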